## Abstract

The d emographic shift toward an older population is accelerating the prevalence of age-related diseases. Precision geromedicine represents a paradigm shift in targeting the biological processes of ageing to optimise health and healthspan, which likely requires multimodal tailored interventions. PROMETHEUS, as part of the XPRIZE healthspan semi-finalist competition, is an 8-week feasibility and exploratory study including 20 middle-aged-to-older participants who received a multimodal intervention comprising fundamental and augmented interventions. The fundamental interventions include sleep and dietary recommendations; supplementation with whey protein, creatine, and fucoidan; supervised exercise with an exergaming component (dual-task cognitive-physical training); motivational interviewing; and cognitive behavioural therapy. The augmented intervention is further personalised based on predefined gerotypes, reflecting individual ageing patterns beyond chronological age. At baseline, urolithin A, nicotinamide mononucleotide, and/or multivitamin-multimineral were prescribed to participants based on their muscle mass, VO_2_peak, and cognitive performance. At mid-intervention, interventions were adjusted based on individual response, including dose escalation and/or the addition of ergothioneine for inadequate improvement in cognition. Primary outcomes include measures of muscle strength and mass, immune function and cognitive performance, and feasibility indicators such as adherence and trial completion. Secondary outcomes include assessments of other biological, clinical, and digital biomarkers of ageing, as well as qualitative indicators of motivation and personal values. This study is aimed at investigating the recruitment feasibility, safety, adherence, and exploratory outcome trajectories of a multimodal, personalised precision geromedicine intervention protocol based on individual participant’s baseline characteristics and interim responses. These findings will also inform the design of a subsequent 12-month, randomised controlled trial evaluating personalised lifestyle and nutraceutical strategies with the potential to incorporate repurposed pharmacological agents to optimise age-related health outcomes.

## Introduction

As the global population ages, the burden of age-related diseases is creating substantial challenges for healthcare systems worldwide [1]. Central biological processes of ageing, including mitochondrial dysfunction, chronic low-grade inflammation, impaired autophagy, and immune dysregulation, among others, have been identified as modifiable targets for intervention [2]. Precision geromedicine provides a geroscience-grounded framework to optimise health and extend healthspan by targeting underlying mechanisms of ageing. Underpinning this approach, precision geromedicine aligns personalised gerointerventions with personal values, preferences, and behavioural contexts to enhance adherence and effectiveness [3]. The foundation of this approach lies in gerodiagnostics, the systematic assessment of biological, clinical, and digital biomarkers that capture an individual’s ageing trajectory and functional status [4]. These multidimensional data are synthesised into gerotypes, which classify individuals based on dominant ageing mechanisms rather than chronological age alone. Gerotypes enable mechanistically informed stratification, guide the selection of targeted gerointerventions [5], and enable continuous monitoring of treatment efficacy and dynamic adjustments based on individual responses [3]. This personalised approach model is the basis for Healthy Longevity Medicine [6, 7], termed precision geromedicine, and represents a shift from the current paradigm of reactive medicine.

Lifestyle, including diet and physical activity, can modulate fundamental biological processes of ageing [4, 6]. Regular physical activity, adherence to a healthy diet, optimised sleep, and mitigation of lifestyle risk factors (e.g. smoking) are associated with a higher lifespan and healthspan by approximately 4–10 years [7]. Nutraceuticals, encompassing a broad range of compounds, have also shown potential geroprotective effects in clinical trials in humans [8, 9]. Nutraceuticals such as whey protein and creatine can enhance muscle protein synthesis, preserve lean mass, and improve strength, with additive benefits when combined with exercise [10]. Other compounds, including fucoidan and nicotinamide mononucleotide (NMN), have been associated with immune and mitochondrial health [11, 12], ergothioneine with antioxidant and neurovascular protection [13], urolithin A with improved mitochondrial function and muscle endurance [14], and multivitamins with cognitive and metabolic health, particularly in at-risk or nutritionally deficient populations [15].

A shift from conventional unimodal therapies toward multimodal interventions is emerging, as combined strategies may exert additive effects across multiple biological mechanisms of ageing and thereby promote healthspan. Multimodal trials such as the Finnish Geriatric Intervention Study to Prevent Cognitive Impairment and Disability (FINGER) study demonstrated that combining dietary intervention, physical exercise, cognitive training, and vascular risk monitoring preserved cognitive function in at-risk older adults from the general population [16]. In addition to these findings, a population-based cohort study demonstrated that modest combined improvements in sleep, physical activity, and diet quality can achieve meaningful lifespan and healthspan benefits, suggesting that multimodal approaches compared to single domain interventions may be more effective by producing additive effects [17]. However, trials, including the Multidomain Alzheimer Preventive Trial and the DO-Health study, did not find significant improvements in clinical outcomes with their multimodal approach [18, 19]. These inconsistent findings likely reflect substantial inter-individual variability, underscoring the necessity of gerotypes with aligned corresponding gerointerventions.

Here, we present the protocol of the PROMETHEUS (PRecision gerOMedicinE: Tailoring Healthy agEing with lifestyle and nUtraceuticalS) trial, a semi-finalist in the XPRIZE Healthspan competition [20]. XPRIZE is an initiative aimed at accelerating the development of interventions that improve the function of multiple organ systems and extend healthy lifespan. This pilot single-arm clinical trial aims to explore the recruitment feasibility, safety, adherence to protocol, and exploratory efficacy of this personalised multimodal precision geromedicine intervention protocol.

## Methods

### Study design

PROMETHEUS is an 8-week feasibility single-arm trial conducted at the Clinical Trial Centre of the NUS Academy for Healthy Longevity, National University of Singapore (NUS). Twenty participants received a multimodal intervention comprising fundamental and augmented interventions. Figure 1 illustrates the study design. Ethical approval for this trial was granted by the National University of Singapore Institutional Review Board (NUS-IRB-2025–393), and the study has been registered at ClinicalTrials.gov (NCT07451496).

**Fig. 1 Fig1:**
[figure not shown]
Study design. Abbreviations: COPD, chronic obstructive pulmonary disease; MVM: multivitamin-multimineral; NIH, National Institutes of Health; NMN, nicotinamide mononucleotide; VO₂peak, peak oxygen uptake. Created in BioRender

### Participant recruitment

#### Pre-screening

Participants were recruited through different social media channels and community engagement events hosted by the NUS Academy for Healthy Longevity. Adults aged 50 to 80 years who had not engaged in regular structured exercise during the past 12 months were considered potentially eligible. Those who expressed interest were directed to the study website to complete a digital pre-screening questionnaire assessing demographics, lifestyle, and medical history after providing written informed consent for pre-screening data collection (Table 1).

**Table 1 Tab1:** Criteria for recruitment

Criteria	Description
Pre-screening inclusion	Aged 50–80 years (both male and female)
	Relatively healthy (have maximum two stable chronic conditions)
	Not engaged in regular resistance or aerobic training in the past 12 months (i.e. untrained)
Inclusion	VO_2_peak below the 75th percentile for age- and sex-specific normative values
	Cognitive performance below the 75th percentile on the NIH Toolbox Cognitive Battery
	Willing and able to comply with exercise and supplementation protocols
	English-literate (can read and understand English)
	Provides written informed consent
	Deemed to have mental capacity, as assessed by the principal investigator
	Able to attend all research visits at MD11, Yong Loo Lin School of Medicine, NUS: screening (~ 2 h), 3 study visits (~ 4–5 h each, 4 weeks apart), 2 interim online visits (~ 45 min), 2 ethics interviews (~ 30 min each), and 3 supervised exercise sessions per week (45 min each)
Exclusion	Significant change in medication in the past 3 months
	History of a major cardiovascular disease (e.g. coronary artery disease, heart failure, and stroke)
	More than two stable chronic conditions (e.g. hypertension, hyperlipidaemia, hyperglycaemia, osteopenia/osteoporosis, osteoarthritis, chronic obstructive pulmonary disease, and type 2 diabetes)
	Known allergies to soy, shellfish/seaweed, mushrooms, or supplement ingredients
	Participation in another interventional clinical trial
	Current use of any study-related supplement unless willing to stop
	Any condition deemed by the principal investigator to jeopardise the safety or study compliance
	Pregnant or planning pregnancy during the study period

*NIH*, National Institutes of Health; *NUS*, National University of Singapore

#### Eligibility criteria

Participants were eligible for inclusion if they satisfied the following criteria: (1) 50 to 80 years old, (2) have not engaged in regular structured exercise during the past 12 months, (3) are relatively healthy (have maximum two stable chronic conditions), (4) have a peak oxygen uptake (VO_2_peak) below the 75th percentile for age- and sex-specific normative values [21], and (5) have cognitive performance below the 75th percentile on the NIH Toolbox Cognitive Function Battery [22].

Participants were excluded if they (1) experienced a significant change in medication within the past 3 months; (2) have a history of major cardiovascular disease such as coronary artery disease, heart failure, or stroke; (3) have more than two stable chronic conditions such as hypertension, hyperlipidaemia, hyperglycaemia, osteopenia/osteoporosis, osteoarthritis, chronic obstructive pulmonary disease, or type 2 diabetes; (4) have known allergies to soy, shellfish/seaweed, mushrooms, or any study supplement ingredients; (5) are participating in another interventional clinical trial; (6) are currently consuming any study-related supplements unless willing to discontinue them for the duration of the study; (7) have any condition that, in the opinion of the principal investigator, may compromise participant safety or study compliance; and/or (8) are pregnant or planning to become pregnant during the study period (Table 1).

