#### Screening and enrolment

Participants who met the eligibility criteria and did not fulfil any exclusion criteria during pre-screening were invited to attend an in-person screening visit. At the screening visit, participants received detailed information about the study’s purpose, procedures, risks, and requirements and provided written informed consent. Recruitment commenced in July 2025 and finished in December 2025. The final participant completed the last study visit on 23 February 2026. The study is currently in the biomarker measurement and analyses phase.

Participants were assessed at baseline, during which they underwent evaluations of muscle mass and function, cognitive function, immune function, biological markers, anthropometric measurements, and clinical and digital measurements. Follow-up assessments were conducted at the mid-intervention (week 4) and at the end-of-intervention (week 8), as shown in Table 2.

**Table 2 Tab2:** Overview of assessments performed at each study visit

Measurement	Pre-screening	Screening	Baseline	Week 4	Week 8
**Informed consent**	•	•			
**Lifestyle and medical questionnaire**	•				

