**Cognitive function**					
National Institutes of Health Toolbox		•		•	•

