**Questionnaires**					
Socio-demographic survey		•			
Wellness questionnaire			•	•	•
Depression Anxiety Stress Scale-21 items			•	•	•
Three-day food diary			•		•
Quality of life					
EuroQol 5-Dimension 5-Level			•	•	•
Short Form 36 Health Survey			•	•	•
Reproductive health					
Androgen Deficiency in Aging Males			•	•	•
Brief Sexual Function Inventory			•	•	•
Female Sexual Function Index			•	•	•
Oral health					
Geriatric Oral Health Assessment Index			•	•	•
Centers for Disease Control and Prevention			•	•	•
American Academy of Periodontology			•	•	•
**Qualitative interviews**			•		•

VO_2_peak was assessed using a cardiopulmonary exercise test (CPET) conducted on an electronically braked cycle ergometer, following a standardised warm-up and an incremental ramp protocol until volitional exhaustion [21] supervised by a research assistant and/or an exercise physiologist. Prior to testing, three blood pressure readings and a temperature measurement were taken to ensure that the risk of adverse events during the test is minimal. If a participant’s blood pressure was elevated, a waiting period of 10–15 min was provided before repeating the measurement. If the blood pressure remained high, the participant was asked to reschedule the session to another day. Participants with an elevated temperature were similarly required to reschedule. Additionally, during the screening visit, cognitive function of the participants was assessed using the NIH Toolbox Cognition Battery, specifically the fluid cognition composite score and the corresponding age-corrected fluid percentage score [22].

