NMN	300 mg/day given if VO_2_peak (mL/kg/min) is below the 50th percentile for age and sex normative data	600 mg/day given if VO_2_peak (mL/kg/min) improvement is below 0.6 for men or 0.7 for women	Normative values in Chinese adults [21]. The cut-off threshold for dose escalation comes from scaled values based on the 10–20 years younger target in the planned 1-year intervention	NMN is safe up to 900 mg/day for 60 days [28]. NMN is a precursor of NAD⁺, a key cofactor in cellular metabolism [11]. Increasing NAD⁺ levels enhances mitochondrial function, energy metabolism, and physical performance, including improvements in aerobic capacity (as measured by VO₂peak) [44]
Multivitamin-multimineral	1 tablet given if cognitive performance score is below the 50th percentile for age and sex normative data based on the NIH Toolbox Cognition Fluid Composite score [45]	Continue dose as baseline	NIH Toolbox Cognition Battery database	Multivitamin-multimineral supplementation is widely used globally and helps correct subclinical micronutrient deficiencies that may impair cognitive function and immune health [45]. Adequate micronutrient status is essential for neuronal function, neurotransmitter synthesis, and immune regulation [15]
Ergothioneine	Not prescribed	25 mg (3 times per week) given if cognitive performance score improvement is below 1.3 for men or 1.0 for women [30]	NIH Toolbox Cognition Battery database	Three times 25 mg per week ergothioneine supplement was safe and induced significant improvement in previous clinical trial [30], and its combination with exercise also showed additive benefit on cognition [13]

*ATP*, adenosine triphosphate; *NAD*, nicotinamide adenine dinucleotide; *NIH*, National Institutes of Health; *NMN*, nicotinamide mononucleotide; *VO*_*2*_*pe**ak*, peak oxygen uptake

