### Statistical and analytical plans

Adherence to each intervention component (sleep, dietary recommendation, supplementation, and exercise) will be analysed descriptively. Adherence will be summarised across the intervention period using mean and standard deviation (SD) or median and interquartile range (IQR) where appropriate. Adherence will be additionally categorised using a predefined threshold of ≥ 80% to indicate adequate adherence. The proportion of participants meeting this threshold will be reported for each intervention component.

Changes in outcome measurements at the mid-intervention and the end-of-intervention compared to baseline will be calculated for each participant. Continuous outcomes will be summarised as mean changes with 95% confidence intervals (CIs) for approximately normally distributed data or as median changes with interquartile ranges (IQRs) for non-normally distributed data. Within-participant changes from baseline to each follow-up timepoint will be assessed using paired t-tests or Wilcoxon signed-rank tests, as appropriate.

To evaluate longitudinal changes across all study timepoints while accounting for within-participant correlation, linear mixed-effects models will be applied for continuous outcomes. Timepoint will be included as a fixed effect, and participant ID will be included as a random effect. Estimated marginal means and corresponding 95% CIs will be reported for each timepoint, together with model-based contrasts comparing mid- and end-of-intervention with baseline.

To account for multiple testing across outcome measures, the Benjamini–Hochberg procedure will be applied to control the false discovery rate. All statistical tests will be two-sided, given the small sample size (*n* = 20), *p* values will be interpreted descriptively and hypothesis-generating only, and 95% CIs will be reported where applicable to support estimation of effect magnitude and precision.

Data will be visualized in spaghetti plot to display the changes during the intervention trajectory at individual level and the group level. All data analysis and visualization will be performed using R.

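### For VO2peak and cognition, Table 2 makes the selecting screening value the baseline, so the planned change from baseline carries a modest, undisclosed regression-to-the-mean gain

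*Protocol article*

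**What the plan says.** Entry depends on two upper limits, both in the Eligibility criteria section and Table 1. Participants must "4) have a peak oxygen uptake (VO_2_peak) below the 75th percentile for age- and sex-specific normative values" and must "5) have cognitive performance below the 75th percentile on the NIH Toolbox Cognitive Function Battery".

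Table 2 marks VO2peak and the row "National Institutes of Health Toolbox" at screening, week 4 and week 8, and leaves the baseline column empty for both. The other primary measures (1RM, ultrasound, CD4/CD8 ratio) are marked at baseline in the same table. The paragraph after Table 2 agrees for cognition: "during the screening visit, cognitive function of the participants was assessed using the NIH Toolbox Cognition Battery".

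The prose under Screening and enrolment differs: "Participants were assessed at baseline, during which they underwent evaluations of muscle mass and function, cognitive function". For cognition this conflicts with Table 2. For muscle function the 1RM test satisfies the wording, so it is no evidence of a second VO2peak test.

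The Primary outcomes section lists VO2peak and the NIH Toolbox Fluid Composite as changes from baseline. Under Statistical and analytical plans, "Changes in outcome measurements at the mid-intervention and the end-of-intervention compared to baseline will be calculated for each participant". The changes are tested with paired t or Wilcoxon tests and modelled with timepoint as fixed effect and participant as random effect. The Discussion gives small sample, short duration and no control arm as limitations and calls the observed changes exploratory.

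**The concern.** A single test result partly reflects luck on the day. If people are admitted only when that result is below a ceiling, those who scored high by chance are turned away and those who scored low by chance are kept. On retest the chance part averages out and the group mean rises, even with no effect of treatment. A control arm selected in the same way would show the same rise; this trial has none.

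If the screening value is time zero, two primary outcomes are therefore biased toward improvement even when the plan is followed exactly. 1RM, ultrasound and CD4/CD8 ratio are not eligibility criteria and are measured at the baseline visit, so they do not share this direct mechanism. At stake is how far the mean changes and their confidence intervals for VO2peak and cognition can be read as response to the programme.

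**Working it through.** The article states no SD, reliability or effect size, and N = 20 follows the competition guideline, so there is no planned figure to reproduce.

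**From the document:** ceiling at the 75th percentile for both tests; n = 20; no control arm; time-only model.

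**Assumed:** normal scores; test-retest correlation r from 0.7 to 0.9; SD 15 points for cognition and 5 mL/kg/min for VO2peak; mean of the screened pool at the norm, or 0.5 or 1 SD below it.

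**Step 1, mean of those selected.** The ceiling is z = 0.674. For a pool with mean m (in SD units from the norm), put c = 0.674 − m. The selected group then lies λ = φ(c)/Φ(c) SD below its own pool mean.
- m = 0: λ = 0.3178/0.75 = 0.424
- m = −0.5: λ = 0.2002/0.8799 = 0.227
- m = −1: λ = 0.0982/0.9530 = 0.103

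**Step 2, expected change with no true effect**, λ × (1 − r), in SD:

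| Pool mean | r = 0.7 | r = 0.8 | r = 0.9 |
|---|---|---|---|
| at norm | 0.127 | 0.085 | 0.042 |
| 0.5 SD below | 0.068 | 0.045 | 0.023 |
| 1 SD below | 0.031 | 0.021 | 0.010 |

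**Step 3, in units, pool at the norm.**
- Cognition: 15 × (0.127, 0.085, 0.042) = 1.9, 1.3, 0.6 points.
- VO2peak: 5 × the same = 0.64, 0.42, 0.21 mL/kg/min.

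A pool above the norm would give more (0.5 SD above: λ = 0.690, so 0.07 to 0.21 SD). The article does not show where the screened volunteers lay.

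**Step 4, against sampling error.** At r = 0.8 the simulated SD of an individual change after selection is 0.617, so the standard error at n = 20 is 0.617/√20 = 0.138 SD. The bias is 0.085/0.138, about 0.6 standard errors. In simulation with no true change and the pool at the norm, a two-sided paired t-test at an assumed 0.05 level rejects in 11.2%, 9.2% and 7.2% of trials for r = 0.7, 0.8 and 0.9.

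**Step 5, can the model correct it?** Fitted to the 20 enrolled people, no: every time-zero value is a selected one. Adding everyone screened helps, because selection then depends on observed data, but eligibility used both tests. With an assumed correlation of 0.3 between true VO2peak and true cognition and r = 0.8, a correction using only the outcome's own screening value overshoots by about 0.02 to 0.03 SD. Conditioning on both screening values brings the bias to zero within simulation error.

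**The case against.** The best reply is that the effect is small and already covered. Only the top quarter is cut off. Participants had not trained for 12 months, so a VO2peak pool below the norm is plausible and the shift shrinks. P values are declared descriptive, and the absent control arm is acknowledged. Finally, the prose under Screening and enrolment may mean that a separate baseline cognition test exists, in which case the whole-group bias for cognition disappears.

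Most of this stands and sets the severity. It does not remove the point: a descriptive p value leaves a biased mean where it is, and a general remark on the missing control arm does not tell readers that two of the primary outcomes carry a bias of known direction.

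Three stronger readings are tempting, and the document does not support them.
- **That the bias swamps the week-4 rule.** A mean shift near 1.3 points invites comparison with the Table 3 rule, "25 mg (3 times per week) given if cognitive performance score improvement is below 1.3 for men or 1.0 for women". Table 3 gives no scale for those figures, while the article records both a composite score and an age-corrected percentage score. The rule also applies to individuals, where noise dominates: at r = 0.8 and SD 15, the share reaching 1.0 or 1.3 by chance rises only from 46% and 45% to 51% and 50%.
- **That results for those below the 50th percentile are much worse.** The shift would be larger there, 0.80 × (1 − r) SD, but no analysis by supplement group is planned.
- **That an inflated effect will size the later randomised trial.** The abstract says the findings will inform its design. The Sample size section says that this sample supplies recruitment rates and outcome variability; it does not mention an effect size.

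**Conclusion.** The concern holds on the schedule in Table 2. The planned change from baseline in VO2peak and NIH Toolbox cognition contains an upward regression-to-the-mean component that the analysis does not remove and the limitations do not name. With r of 0.7 to 0.9 it is about 0.04 to 0.13 SD for a pool at the norms (about 0.6 to 1.9 cognition points at SD 15, or 0.2 to 0.6 mL/kg/min at SD 5) and about 0.01 to 0.07 SD for a pool 0.5 to 1 SD below them. All SDs, reliabilities and pool means are assumptions. The direction is firm and the size modest. It should be fixed, but it does not undermine the feasibility aims or the other primary measures. For cognition it also depends on how the conflict between the prose and Table 2 is resolved.

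**What to change.** 1. Reconcile the prose under Screening and enrolment with Table 2, and label time zero as screening for VO2peak and the fluid composite. If a separate baseline cognition test exists, use it as time zero.
2. Otherwise, report the expected regression-to-the-mean shift beside each observed change, over a stated range of r and of the screened pool's mean, and name it in the limitations.
3. Where screen-failure values are available, add a sensitivity analysis with all screened people at time zero. Model VO2peak and cognition jointly, or condition on both screening values, and allow for the age and sex norms behind the cut-offs. State that the estimate refers to the screened population, including people who were never treated.
4. The week-4-to-week-8 contrast avoids the selected value but covers only the second half, after interventions were adjusted. Show it as a supplement only.

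The article reports the study as still in its measurement and analysis phase, so this needs wording and screening data already collected, with no new visits. The sensitivity analysis costs some precision: in a single-criterion simulation at r = 0.8 the SD of the estimate rose from 0.138 to 0.144 SD units, about 4%. The reported gains would be somewhat smaller.
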